#### Secondary objectives

The secondary objectives are as follows:Clinical○ Determine the relative effect on quality of life (QoL) amongst trial participants○ Measure overall satisfaction with prophylactic antibiotic treatment○ Assess participants’ perception of benefit at 12 months using qualitative methodology○ Record adverse effects related to both prophylaxis and treatment antibiotic use○ Determine relative rates of hospitalisation because of UTI○ Measure difference in renal function by estimated glomerular filtration rate (eGFR) at 12 months○ Determine rates of asymptomatic bacteriuria at 12 months○ Assess ecological change in *E. coli* isolated from urine and perianal swabsEconomic○ Measure incremental cost per QALY gained through repeated completion of SF-36○ Assess participants’ willingness to pay to avoid a UTI by contingent valuation at end of trial participation and incorporate these data in the economic evaluation using a cost-benefit framework.

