### Secondary outcome measures

Secondary outcome measures will be collected as additional criteria to the primary outcome from inspection of participant healthcare records, by participant questionnaire or by clinical test performed at specific time points. The following are also included.The rate of UTI will also be alternatively defined as the *incident density rate*; the number of UTIs suffered during the observation period minus days spent taking treatment courses of antibiotics active against urinary tract organisms.*Febrile UTI* defined as the primary outcome plus presence of a recorded fever of more than 38 °C:○ Confirmed by inspection of primary or secondary healthcare record by research staff.*Microbiologically confirmed symptomatic UTI* defined as the primary outcome plus positive urine culture:^1^○ Participants will provide an intermittent catheter specimen of urine for local analysis as requested by the treating clinician. This will be analysed according to clinician decision by the local microbiology using the local standard operating procedure (SOP). We will also ask the participant to send a urine specimen using provided safe packaging to the central microbiology trial laboratory in the Newcastle upon Tyne Hospitals NHS Foundation Trust each time they consider they have symptoms suggestive of UTI and intend to commence a course of antibiotic treatment. This will be analysed and cultured on receipt and the result used for trial outcome purposes but not for patient care.*Antibiotic prescription for asymptomatic UTI* without participant-reported or clinician recorded evidence of symptom change.*Asymptomatic bacteriuria* defined as a positive urine culture in the absence of symptoms.○ Participants will be asked to send a urine sample to the central laboratory at baseline prior to randomisation and during asymptomatic periods in months 3, 6, 9 and 12 of their trial participation. They will also be separately consented to provide a urine sample 6 months after completion of trial (18-month time point).*Hospitalisation due to UTI* defined as an unplanned visit to hospital for treatment of a UTI which required at least one overnight stay in hospital.○ Collected from healthcare record review and checked from participant report or enquiry.*Participant perception of benefit.*○ We will record and analyse semi-structured interviews with up to 30 participants purposively sampled from both trial arms on completion of their 12-month trial period.*Overall satisfaction with allocated treatment strategy.*○ Participants will complete the treatment satisfaction questionnaire for medication at 12 months as part of their completion of trial questionnaire [20].*Generic health-related quality of life.*○ Participant completion of the SF-36 1-week recall questionnaire at baseline, 3, 6, 9 and 12 months and within the first 2 days of each episode of symptomatic antibiotic-treated UTI [21].

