
#### Adverse effects (harms)

The adverse effects are as follows.*Adverse effects of antibiotic therapy*○ During antibiotic prophylaxis use▪ Collected by participation checklist completed at 3, 6, 9 and 12 months▪ Recording of relevant data from primary and secondary care records at 12 months○ During treatment antibiotic use▪ Collected as part of participant log during episode of antibiotic-treated UTI▪ Recording of relevant data from primary and secondary care records at 12 months*Change in renal function* defined as estimated creatinine clearance measured by serum creatinine blood test at baseline before randomisation and during an asymptomatic period in month 12*Change in liver function* defined as clinically significant change in liver function indices measured by serum liver function tests (LFTs) at baseline and at 12 months*Bacterial ecological changes* to type and resistance patterns of *E. coli* isolated from urine specimens and perianal swabs analysed at the central laboratory at baseline prior to randomisation and at 3, 6, 9 and 12 months after randomisation and from surveillance of other urine specimens submitted to the central laboratory. Participants will also be separately consented to provide a urine specimen and perianal swab together with an antibiotic use questionnaire 6 months after completion of trial (18-month time point).

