### Statistical analysis

An analysis of the primary outcome measure (incidence of UTI) for the full study will be performed both for the full data set and for the separate sub-groups defined by high and low baseline UTI rate (as specified during stratification for the randomisation process) using both the Poisson rate test and an incidence density ratio approach to allow for the different treatment durations; regression or generalised linear modelling approaches will be used to adjust for the effects of covariates. The model selection process will include the stratification factors (prior rate of UTI, presence of neurological disease and gender) and other baseline variables (person doing CISC [self or other], asymptomatic bacteriuria, age, type of catheter, use of antibiotic prophylaxis for UTI in the previous 12 months prior to randomisation and presence of bladder augmentation). The inclusion of interaction terms such as site will also be explored. The inclusion of baseline values as covariates will additionally enable the examination of possible interactions between effects observed and these values. Not all covariates mentioned above will be included in the final model, but all will be considered during the model selection process.

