A number of additional secondary analyses will also be undertaken to examine the secondary outcome variables. Febrile and microbiologically confirmed UTI, asymptomatic bacteriuria and hospitalisation due to UTI will be analysed in a manner analogous to that for the primary outcome. Analyses of other outcomes will use similar regression or analysis of variance/covariance-based approaches as described above to compare between treatment groups while allowing for the effects of covariates. Baseline measures would be included in the analysis, either considered as possible covariates or by exploring changes in outcome measures from baseline. Analysis will be carried out primarily on an intention-to-treat basis, although other exploratory analyses such as per-protocol may also be considered. Data will be analysed at the end of the study; there are no planned interim analyses. Safety data will be regularly and frequently reviewed but will not be subjected to statistical analysis. Data with missing observations due to loss to follow-up will be examined to determine both the extent of the missing data and whether they are missing at random or are informative. If data are missing to a sufficient extent, the use of appropriate multiple imputation techniques will be considered.

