### Study monitoring

Quality control will be maintained through adherence to SOPs published by the Newcastle CTU, study protocol, the principles of GCP, research governance and clinical trials for investigational medicinal products regulations. An independent Data Monitoring and Ethics Committee (DMC) has been convened to undertake independent review. The purpose of this committee will be to monitor efficacy and safety endpoints, and it will operate according to written terms of reference linked to the DAMOCLES charter [35]. Only the DMC will have access to full unblinded study data, if requested, prior to completion of the trial. All analyses will follow a carefully documented statistical analysis plan. The TSC and DMC will be asked to review and comment on this plan prior to analysis. A single main analysis will be performed at the end of the trial when all follow-up has been completed. The DMC will meet initially to agree on terms of reference and other procedures. The final trial report will contain full details of the analytical methodology. The DMC will meet at least three times: at the start, middle and completion of the study. At the first meeting, the committee will agree on its charter of operation and discuss and advise on criteria for the need for interim analysis and adoption of a formal set of stopping rules for efficacy or safety.

A Trial Steering Committee (TSC) has been established to provide overall supervision of the trial. The committee will meet approximately every 6 months during recruitment and annually thereafter for the duration of the trial.

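### For continuous secondary outcomes, baseline may enter as an optional covariate or through a change score; fixing baseline-adjusted analysis would be more precise at no cost

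*Protocol article*

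**What the plan says.** The protocol article, Statistical analysis, assigns febrile and microbiologically confirmed UTI, asymptomatic bacteriuria and hospitalisation to the same methods as the primary outcome. For the rest it says: "Analyses of other outcomes will use similar regression or analysis of variance/covariance-based approaches as described above". It then says how baseline is to be used: "Baseline measures would be included in the analysis, either considered as possible covariates or by exploring changes in outcome measures from baseline".

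The approach to which this refers back is the covariate search for the primary outcome, which ends: "Not all covariates mentioned above will be included in the final model, but all will be considered during the model selection process".

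The main continuous outcomes concerned have baseline values:

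- **Quality of life** (Secondary outcome measures): "Participant completion of the SF-36 1-week recall questionnaire at baseline, 3, 6, 9 and 12 months", and also at each treated UTI.
- **Renal function.** Secondary objectives: "Measure difference in renal function by estimated glomerular filtration rate (eGFR) at 12 months". Adverse effects (harms) lists a change in renal function, "defined as estimated creatinine clearance measured by serum creatinine blood test at baseline before randomisation and during an asymptomatic period in month 12".
- **Liver function** (Adverse effects (harms)): "defined as clinically significant change in liver function indices measured by serum liver function tests (LFTs) at baseline and at 12 months".

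The same Statistical analysis section says that safety data will be reviewed often but not analysed statistically. It does not say whether the month-12 renal and liver tests count as safety data for this purpose.

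**The concern.** Comparing changes from baseline and comparing follow-up values adjusted for baseline estimate the same treatment effect in a randomised trial, but with different precision and different behaviour when the arms differ at baseline by chance. The text allows either, and it makes the better one conditional by calling the baseline value a possible covariate. If the change-score route is taken without adjustment, intervals are wider than the collected data allow, and part of any chance baseline difference is carried into the estimate with the opposite sign.

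At stake is the precision of the quality-of-life comparison and, if it is formally tested, the renal comparison. Both are named secondary objectives, in a trial whose Background asks whether benefit is worthwhile in terms of harms. Renal function has a further difficulty: the objectives and the harms section name different quantities (eGFR; estimated creatinine clearance) and describe the contrast differently (a difference at 12 months; a change).

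**Working it through.** **The plan's own figure.** The article states no power or precision for any continuous secondary outcome. Its primary-outcome sample size supplies the number per arm used below, so I checked that first.

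- Inputs (Sample size calculation): rates of 3 and 2.4 per year, 90% power, 5% level, 15% attrition. Two-sided testing is assumed.
- n per arm = (1.960 + 1.2816)² × (3 + 2.4) / 0.6² = 10.507 × 15 = 157.6, so 158.
- Total = 316 / 0.85 = 371.8, so 372.

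Both figures reproduce, and nothing in this point touches them.

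**Variance of the treatment effect.** Assume equal SD at baseline and follow-up, one follow-up time, and baseline-to-follow-up correlation r. In units of 2·SD²/n:

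- unadjusted change score: 2(1 − r)
- ANCOVA on the follow-up value: 1 − r²
- ratio, change to ANCOVA: 2(1 − r) / [(1 − r)(1 + r)] = 2/(1 + r)

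The documents give no r, so a range is shown. An effect with 90% power under ANCOVA lies 3.2415 standard errors from zero. Under the change score its power is Φ(3.2415/√ratio − 1.96).

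| Assumed r | Change | ANCOVA | Ratio | Power with change score |
|---|---|---|---|---|
| 0.5 | 1.00 | 0.75 | 1.33 | Φ(2.807 − 1.96) = 80% |
| 0.7 | 0.60 | 0.51 | 1.18 | Φ(2.989 − 1.96) = 85% |
| 0.8 | 0.40 | 0.36 | 1.11 | Φ(3.075 − 1.96) = 87% |

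Outside that range the ratio is 1.54 at r = 0.3 and 1.05 at r = 0.9.

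**Chance imbalance.** With 158 per arm, the baseline difference has standard error √(2/158) = 0.113 SD, so it falls within ±1.96 × 0.113 = ±0.22 SD in 95% of trials. A baseline difference d moves the change-score estimate by −(1− r)d. For d = 0.1 SD that is −0.05 SD at r = 0.5 and −0.02 SD at r = 0.8. ANCOVA is not shifted.

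**If baseline dropped out altogether.** A comparison of follow-up values alone has variance 1 in the same units, and 1/(1 − r²) relative to ANCOVA: 1.33 at r = 0.5 and 2.78 at r = 0.8. This would be the larger loss, but the article does not list it as an option (see the objection).

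**SF-36.** These formulas describe a single follow-up time. The SF-36 has four scheduled ones, so for it the figures are a guide to each time point, not to a repeated-measures analysis.

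**The case against.** The strongest reply is that this belongs to the statistical analysis plan. The article says: "All analyses will follow a carefully documented statistical analysis plan", and the steering and data monitoring committees are asked to comment on it before analysis. ANCOVA is among the approaches named, nothing obliges the analyst to use a poorer one, and a change score that is itself adjusted for baseline gives the same treatment effect as ANCOVA. All of this stands, and it makes the loss possible rather than certain. It does not remove the point, because the article states an either/or and calls the baseline value optional.

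Three stronger readings are tempting and are not supported:

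- **A baseline-free 12-month comparison is planned.** A reader might infer this from the renal objective together with the rule that not all covariates are kept. But the analysis sentence says that baseline would be included. The objective names a time point, and a baseline-adjusted estimate is also a difference at 12 months. The selection rule is written for the listed primary-outcome covariates, which do not include baseline SF-36, eGFR or liver tests. That it carries over to these outcomes is an inference.
- **The false-positive rate is about 9% to 10%.** Simulation gives that if the most favourable of the follow-up-only, change and ANCOVA results is quoted at a nominal 5%, and about 7% for the better of change and ANCOVA. Either needs selective reporting, which the pre-reviewed plan and analysts kept unaware of allocation as far as possible are there to prevent.
- **Liver function should become a comparison of means.** A few marked elevations hardly move a mean, so demoting clinically significant change could hide the harm of interest. Its threshold may properly sit in the full protocol or analysis plan.

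**Conclusion.** The point holds as a cost-free improvement to the analysis of secondary outcomes. The article permits an unadjusted change score where ANCOVA on the same data is more precise and is not shifted by chance baseline differences. For an assumed correlation of 0.5 to 0.8 the cost is 33% to 11% more variance, or 90% power falling to about 80% to 87%. At high correlations the cost is small. These figures assume equal SDs, a single follow-up and no baseline adjustment of the change score. A larger loss would follow only if the baseline value were dropped during model selection, which the article does not state.

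Separately, the two descriptions of renal function need aligning on the named quantity and contrast. The statement about not analysing safety data also needs a stated scope: if it covers month-12 renal function, it conflicts with the renal objective; if it does not, the choice of estimator is open. The primary outcome and the sample size are unaffected.

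**What to change.** In Statistical analysis, replace the either/or with one rule. Each continuous secondary outcome that is formally compared and has a baseline value is analysed on its follow-up value, with its own baseline value and the three stratification factors always in the model. Change scores are descriptive only. For SF-36 scores, add that the repeated follow-up times are handled within the model. For renal function, the follow-up value is the month-12 value.

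Make Secondary objectives and Adverse effects (harms) agree on the renal quantity (eGFR or estimated creatinine clearance) and on the contrast. State whether the sentence on safety data covers the month-12 renal and liver tests. Keep clinically significant change as the liver outcome.

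The cost is wording only, since the baseline values are already collected. If the statistical analysis plan already fixes this, confirming it and aligning the protocol text is enough.

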### Economic analysis

Analyses will be carried out from the perspective of the UK NHS and personal and social services, but we will also take a wider perspective by including costs borne by the participants and their families. All unit costs will be derived using routine data sources [28] and study-specific estimates. Where appropriate, discounting will be applied to costs and outcomes at UK recommended rates [29]. Data on use of services will be combined with appropriate unit costs to produce a cost for each trial participant. From these a mean cost per intervention and a mean cost taking into account patient and carer costs will be estimated. Results for cost-effectiveness will be presented as point estimates of mean incremental costs and effects. The within-trial analysis will also compare changes in health-related quality of life (HRQoL) based on responses to the SF-36 and converted into the SF-6D [30] to estimate quality-adjusted life years (QALYs) using the area under the curve approach. They will subsequently be used in a cost-utility analysis based on avoidance of UTI. The results will be presented as point estimates of mean incremental costs and QALYs. Both cost-effectiveness and cost-utility analyses will include deterministic and stochastic sensitivity analyses, presented as point estimates and cost-effectiveness acceptability curves.

A contingent valuation study at 12 months will collect individuals’ willingness to pay for a reduction in the number of UTIs. For a given level of income, higher monetary values indicate that they would derive greater benefit. This method will enable us to place a monetary value on the health outcome, going beyond the QALY framework, and also to conduct a cost-benefit analysis. The cost-benefit analysis expresses both costs and benefits in commensurate units, which enables a comparison to be made between strategies [31]. The decision rule for the cost-benefit analysis is therefore relatively simple: if the benefits measured in pounds sterling (£) exceed the costs, this represents a gain in welfare and the strategy is deemed worthwhile [32]. Results will be presented as incremental net benefits (net benefits = mean willingness to pay – mean cost of intervention). Both stochastic and deterministic sensitivity analyses will be conducted and the results presented as incremental net benefit curves and as the probability that each treatment would be considered cost-effective.

### Sample size calculation

We plan to recruit 372 participants to the trial. Based on systematic reviews [11, 14] and expert (including patient) opinion, we believe that an overall 20 % reduction in symptomatic UTI rate from an average of 3 to 2.4 episodes per year represents the minimum clinically important difference. Using the Poisson rate test, completion of the study by 158 participants in each arm, 316 in total, would give 90 % power to detect this difference at the 5 % level. A total of 372 would allow for a 15 % attrition rate estimated from previous trials included in the systematic review. The attrition rate will be monitored and the sample size increased if necessary. Half this sample size would give 92 % power to detect a 25 % difference in the high frequency sub-group (from 4 to 3 episodes per year) and more than 99 % power for a 50 % reduction in the low frequency group (from 2 to 1) without allowance for multiple testing. We will approach approximately 750 eligible patients, anticipating a 50 % recruitment rate. We are currently recruiting from 52 sites which are coordinated through seven trial hubs. This number will be adjusted according to site and overall recruitment rate. For the qualitative sub-study of participant perception of benefit we will interview 30 trial participants who, at the time of trial consent, expressed a willingness to be interviewed at completion. We will create a purposive sample of approximately 20 participants from the prophylaxis arm and 10 from the no prophylaxis arm including some with neurological disease and some who did not complete the trial as allocated. We anticipate this will be sufficient to saturate themes arising from qualitative analysis of interview transcripts. For contingent valuation we will use a sample of 100 participants in each group; 200 in total will complete an exit questionnaire.

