In a large RCT of antibiotic prophylaxis of recurrent UTI in women with normal voiding, it was found that faecal and urinary carriage of resistant *E. coli* was increased from 40 % to 80 % by use of trimethoprim-sulfamethoxazole once daily prophylaxis but that this returned to baseline 3 months after discontinuing of the antibiotic prophylactic therapy [17]. There remains public health concern regarding the empiric prophylactic widespread use of antibiotics given the rapid emergence of resistant strains of bacteria, including *E. coli*. Antimicrobial stewardship, including the appropriate use of antimicrobial prophylaxis, has become a priority.

This background has led us to design a robust pragmatic trial to determine whether the apparent benefit of antibiotic prophylaxis seen in small trials amongst specific groups of CISC users is also seen in a routine care setting and whether the benefits are worthwhile in terms of harms. The estimates of prevalence, effectiveness and harms have allowed us to power the trial conservatively based on what we consider to be a minimum important difference from clinician, patient and economic perspectives.

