#### Target population and sample size

We will recruit from the population of adult users of CISC. The setting is NHS hospitals and community sites throughout the UK where CISC use is taught and monitored. We expect to randomise at least 372 participants over a 28-month period. For primary outcome purposes, follow-up will continue for 12 months after randomisation. Participants will be given the option of submitting an additional urine and perianal swab sample 6 months after trial completion (18-month time point) to assess return to baseline of *E. coli* ecology. Separate consent will also be asked for permission to access clinical records for extended follow-up for a further 9 years (10 years in total) and for life-long linkage to central NHS databases.

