### Randomisation

#### Participant allocation

Randomisation will be administered centrally by the Newcastle Clinical Trials Unit secure web-based system. Permuted random blocks of variable length will be used to allocate participants 1:1 to the control and experimental groups and ensure concealment of allocation from central trial staff. An individual not otherwise involved with the study will produce the final randomisation schedule. Stratification by three variables: (1) prior frequency of UTI: <4 episodes per year and ≥4 episodes per year, (2) a diagnosis of neurogenic lower urinary tract dysfunction: yes or no and (3) sex: female or male, will be performed prior to randomisation to ensure balanced allocation within these factors. For those allocated to prophylaxis an appointment will be arranged, facilitated by trial staff, with the prescribing clinician to commence prophylaxis. This may be a hospital consultant, a GP or a nurse specialist. Continued supply will be ensured typically through repeat prescription from the individual participant’s GP.

Patients may only be randomised into the study by an authorised member of staff at the study research site, as detailed in the delegation log.

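### The stated 90% and 92% power assume pure Poisson counts, so they hold only if UTI rates do not vary between patients within strata

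*Protocol article*

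**What the plan says.** The *Sample size calculation* section sizes the trial on a fall "from an average of 3 to 2.4 episodes per year". The test and the number of completers are given as follows: "Using the Poisson rate test, completion of the study by 158 participants in each arm, 316 in total, would give". The power claimed for that comparison is 90%, at a 5% significance level. The section then inflates 316 to 372 for 15% attrition. A second figure, 92%, is stated for half the sample and is the "power to detect a 25 % difference in the high frequency sub-group (from 4 to 3 episodes per year"). For a fall from 2 to 1 in the low-frequency group the stated power exceeds 99%. No standard deviation, dispersion or other allowance for variation between patients is given.

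The *Statistical analysis* section names the Poisson rate test and an incidence density ratio for the primary outcome, overall and in the two frequency subgroups, with regression or generalised linear models to adjust for covariates. Prior UTI frequency (below 4, or 4 and above), neurogenic dysfunction and sex are randomisation strata (*Participant allocation*). They enter model selection with other baseline variables, not all of which will be kept.

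**The concern.** A Poisson calculation treats every patient in a group as having the same underlying rate. The article describes a population in which that is unlikely, even within a prior-frequency stratum:

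- *Target population* admits patients through two or more community-treated UTIs, one severe hospital-treated UTI, or earlier prophylaxis followed by washout.
- The upper frequency stratum has no ceiling.
- *Background* links neurological disease, sex, age and bladder volume to UTI prevalence.
- *Statistical analysis* lists who performs the catheterisation, asymptomatic bacteriuria, catheter type, recent prophylaxis and bladder augmentation as candidate covariates.

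Neurological disease and sex are themselves strata, so adjustment can absorb them. The other sources are not strata.

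If variation remains within strata, a valid analysis has less power than stated, and a null result could be read as a 90%-powered negative when it is not. If the Poisson test is kept uncorrected, the problem moves to the significance level.

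**Working it through.** **Inputs from the article.** Rates 3 and 2.4; 158 completers per arm; subgroup rates 4 and 3, and 2 and 1, with 79 per arm; 1:1 allocation; 12 months' follow-up; 15% attrition. The 5% level is not said to be one- or two-sided. Two-sided reproduces 158; one-sided would give 128.5.

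**1. The stated figures, with variance equal to the mean.**
- n per arm = (1.960 + 1.282)² × (3 + 2.4) / 0.6² = 157.6, so 158.
- Power at 158: Φ(0.6/√(5.4/158) − 1.96) = 90.1%.
- 4 versus 3, 79 per arm: Φ(1/√(7/79) − 1.96) = 91.9%.
- 2 versus 1, 79 per arm: 99.9%.
- 316/0.85 = 371.8, so 372.

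Everything reproduces, so no extra variance was allowed for.

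**2. Does the 4-versus-2 split alone lower the power?** Take equal halves with control rates 4 and 2 and a rate ratio of 0.8.
- Strata ignored: variances are 3 + 1 = 4 and 2.4 + 0.64 = 3.04. Power is Φ(0.6/√(7.04/158) − 1.96) = 81%.
- Stratified: the variance of the difference is (4 + 3.2 + 2 + 1.6)/(4 × 79) = 5.4/158, as in step 1. Power is 90.1%.

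In 20,000 simulated trials with the halves balanced between arms, the plain Poisson test also kept about 90% power and 5% type I error. The split alone therefore costs nothing in a stratified design.

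**3. Residual variation within strata.** Assume variance = mean + k × mean² within each stratum. Here k is the squared coefficient of variation of patients' true rates, so k = 0.1, 0.25 and 0.5 mean coefficients of variation of 32%, 50% and 71%. These values are assumptions; the article gives none.

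Within a stratum, Var(log rate ratio) = (1/μ_control + 1/μ_prophylaxis + 2k)/79. Strata are combined by inverse variance. At k = 0.25:
- Rates 4 and 3.2: (0.25 + 0.3125 + 0.5)/79 = 0.01345.
- Rates 2 and 1.6: (0.5 + 0.625 + 0.5)/79 = 0.02057.
- SE = 1/√(1/0.01345 + 1/0.02057) = 0.0902.
- Power = Φ(0.2231/0.0902 − 1.96) = 70%.
- High-frequency subgroup, 4 versus 3: SE = √((0.25 + 0.3333 + 0.5)/79) = 0.1171. Power = Φ(0.2877/0.1171 − 1.96) = 69%.

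The detectable reduction at 90% power is 1 − exp(−3.24 × SE), with the SE taken at a rate ratio of 0.8.

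**4. The uncorrected Poisson test.** Over the two halves under the null, true variance divided by Poisson variance is (4 + 16k + 2 + 4k)/6 = 1 + 10k/3. Type I error is 2 × (1 − Φ(1.96/√ratio)).

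| k (assumed) | Overall power | 4 vs 3 power | Detectable reduction | Type I error, uncorrected Poisson |
|---|---|---|---|---|
| 0 | 90% | 92% | 20% | 5% |
| 0.1 | 81% | 82% | 22% | 9% |
| 0.25 | 70% | 69% | 25% | 15% |
| 0.5 | 55% | 53% | 29% | 23% |

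Simulation with a single mean rate of 3 gave type I errors of 14% and 22% at k = 0.25 and 0.5. There the uncorrected test rejected in 84% of trials at k = 0.25 with a true 20% reduction. That rate looks close to target only because the test also rejects a true null 14% of the time; a variance-respecting test had 71% power.

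**The case against.** The strongest reply is that nothing is miscalculated. The Poisson basis is disclosed, every figure reproduces, and no k can be found in the document. That stands: this is an unstated condition on the power, not an arithmetic error, and its size is hypothetical.

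It is also fair that the power loss belongs to an overdispersion-allowing analysis, which the article does not name. Under the named Poisson test the main damage is to the 5% level. A separate analysis plan may already deal with this, but the power figures are stated here without the condition.

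A reader might infer more than the documents support:
- *That the paragraph contradicts itself by using rates 4 and 2.* It does not: prior frequency is a stratum and a candidate covariate, and step 2 shows that stratification restores 90%. The paragraph also states no variation within the high-frequency subgroup.
- *That 4 is the floor of the upper stratum and so too low.* The cut-off is a prior-year count and the 4 is an expected rate in the trial, which can fall after selection on a high count.
- *That 4 to 3 and 2 to 1 average to a 33% reduction, against the planned 20%.* They are separate detectable differences, not a joint forecast.
- *That the claim "have allowed us to power the trial conservatively" is wrong.* The sentence ties that word to the minimum important difference, not to the variance.

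**Conclusion.** The point holds as a condition on the stated power. The 90% and 92% require zero unexplained variation in UTI rate within strata. The article gives no support for that and describes several reasons to doubt it. Any residual dispersion lowers the power of a valid test or, if the Poisson test is left uncorrected, raises its type I error.

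How far cannot be derived from the document. Over an assumed k of 0.1 to 0.5, overall power runs from about 81% to 55% and high-frequency subgroup power from about 82% to 53%. Uncorrected type I error runs from about 9% to 22–23%. These figures further assume equal halves with control rates 4 and 2, a common rate ratio of 0.8 for the overall comparison, and a full 12 months for all 316 completers. It would go too far to say that the power has been shown to be overstated by any particular amount.

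**What to change.** 1. In *Sample size calculation*, say that 90% and 92% are conditional on Poisson variance within strata. Add power and the detectable reduction over a stated range of k, as in the table.
2. Extend the existing attrition monitoring with a pooled, blinded tabulation of event rate and dispersion, so that the stated power can be updated before unblinding.
3. Unless the analysis plan already does so, base the primary test on a variance that allows for overdispersion (negative binomial, or Poisson with a robust or scaled variance). Adjust it for the three stratification factors as fixed terms instead of leaving them to model selection.

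Printing subgroup power at a 20% reduction is optional. The cost is some wording and one blinded table. The downside is a less favourable stated power; no extra patients are requested.
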